- A2.2. Administer Life S-Can to all participants at the Clinical Trials Unit by a trained research dietitian. Re-administer after 7-10 days for reproducibility analysis (test-retest method).
- A2.3. Collect data of individual domains using validated questionnaires and objective measurements.
- A2.4. Data integration and statistical analysis to determine relative and construct validity of Life S-Can.

**SA3. Carry out a pilot intervention study in cancer survivors to determine the feasibility, acceptability and efficacy of Life S-Can.**

- A3.1. Recruit an expert panel in the field oncology specialised in diet, physical activity, lifestyle and cancer psychology, as well as cancer survivors (non-scientific actors).
- A3.2. Design a 3-month intervention plan with the expert panel and non-scientific actors, based on tailored sessions and personalized feedback according to Life S-Can answers, with the aim to improve QoL.
- A3.3. Randomize participants from A2.1. to either the intervention group (IG) or control group (CG). Offer a personalised intervention care plan to patients from the IG, based on their answers and score. Continue with standard care in patients assigned to CG.
- A3.4. Arrange appointments for IG patients at the Clinical Trial Unit with trained oncological dietitians, physical activity specialists and psychologists, depending on their answers (1 to 3 sessions, individual and as a group).
- A3.5. Re-administer Life S-Can and collect data on feasibility, acceptability and efficacy to all participants after 3 months since the first administration of Life S-Can (A2.2).
- A3.6. Data integration and analysis.

**SA4. Carry out a qualitative study in cancer survivors and health professionals to design a complex intervention to determine the feasibility and effectiveness of the implementation of Life S-Can in clinical settings.**

- A4.1. Design a qualitative study in a clinical setting (primary care, hospital) together with Key Personnel listed in the project.
- A4.2. Recruit 40 cancer survivors and health care professionals from the Oncology Department at the HUSE and in Primary Care clinics. Organize four focus groups and semi-structured like in-depth interviews (audio-recorded) of a duration of 1 hour.
- A4.3. Transcribe audios, collate data and analyze using thematic analysis.

1. **Type of study**

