If a participant agrees to participate, they will be given an information sheet (HIP_1), an informed consent (CI_1) and ten saliva collection tubes + instructions to take home. Once the participant has agreed to participate in the study, a research dietitian will contact the person to convene a day and time to meet at the Clinical Trials Unit. During this call, the dietitian will briefly explain what the study will entail and will give detailed instructions on how to collect saliva with the tubes previously administered (Salivette swabs for two days, at five different time points: at waking, 30 min after waking, at noon, at 5pm and anytime between 8-10pm).

**Workflow of the validation study (Study 2):** The validation study will consist into three visits to the research/hospital facility. The **first visit** will be at the Clinical Trials Unit, will take approximately 1 h and will be divided into three parts: 1) Administration of Life S-Can; 2) Administration of validated questionnaires; and 3) Obtain objective measurements of the patient. The **second visit** will also be at the Clinical Trials Unit and will take approximately 10-15 minutes. Participants will be asked to return the accelerometer and complete the Life S-Can questionnaire again (reproducibility). The **third visit** will be at the Nuclear Medicine Imaging Unit at the HUSE, for dual-energy x-ray absorptiometry (DXA) imaging. If possible, the second and third visit will be done on the same day, considering that the research facility is located within the hospital.

**1. Administration of Life S-Can to n=100 cancer survivors:** A research dietitian will collect standard sociodemographic and clinical data of each participant and will then administer the Life S-Can screener. Participants will be offered to complete the Life S-Can questionnaire again after 10 days to test for reproducibility (either by phone or in person, to be convened with the patient), based on the test-retest method.

An individual code will be used for each participant (structure: LS-XXX) when completing all questionnaires, which only the principal investigator and research dietitian will be able to trace to the individual. On all electronic databases used in this project, only the code will be used so no other user can identify the identity of the participant. This same code will be used to mark all biological samples (saliva, blood). All questionnaires will be on an electronic platform and completed electronically.

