**3. Obtain objective measurements:**

- **Body weight and height** will be measured by a research dietitian at the Clinical Trials Unit.
- **Physical activity**: Physical activity, sedentary behaviour and sleep quality will be measured using an accelerometer. All participants will be offered to wear an accelerometer for 7 to 10 days. Accelerometry is one of the most reliable techniques for recording and storing the amount and level of physical activity performed by each person and in a given period of time. An accelerometer will be provided to the participant and it will be explained how to use it, and it will have to be returned after 7-10 days. These accelerometers are owned by the NUTRECOR research group and do not imply any added cost for the research group or for the participant. In addition, the use of an accelerometer constitutes a non-invasive technique.
- **Skeletal muscle mass and fat mass** Skeletal muscle mass and fat mass will be determined by a technician from the Nuclear Medicine Imaging Unit using DXA if possible, or using the bioimpedance measurement technique. DXA analysis is of interest to measure skeletal muscle accurately (in this case, for the interest of determining sarcopenia); however, it implicates a small exposure to radiation, similar to that of an X-ray. For this reason, participants will be given the option to either opt out of this procedure and/or analyze body composition via bioimpedance (which is less accurate for muscle mass).
- **Muscle function**: Muscle function will be determined using grip hand strength and the 30-s chair test.
- **Stress** will be measured by cortisol levels in the saliva samples brought in by the patient. Briefly, the salivary samples brought in by the participant will be stored at –80ºC and assayed for cortisol using an enzyme-linked immunosorbent assay kit following the protocol specified by Salimetrics. Samples will be assayed in duplicate.
- **(optional) Blood sample extraction:** All participants will be offered the option to provide a blood sample, which will be centrifuged to obtain blood specimens and will be stored at -80ºC for future studies in this cohort. This will be completely optional and will not determine participant inclusion in the study.

Staff from the Clinical Trials Unit will aid in sample obtention, processing and storing (research technicians) of all biological samples.

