**Data integration and statistical analysis:** All data obtained using the questionnaires and the objective measurements will be integrated into a database. Any additional medical data needed will be obtained through medical records (prior consent by the participant). A data management plan following the FAIR principles will be established. Construct validity will be studied using the hypothetical latent structure, structural equation models and psychometric tests. Pearson correlation and Intraclass correlation and Cohen’s Kappa will be used to test the relative validity, reliability and reproducibility of the screener. Internal consistency of the screener will be analysed using Cronbach Alpha.

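### The protocol gives two modes and two intervals for the Life S-Can retest, so any phone retests would add mode differences to the reproducibility estimates

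*Protocol*

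**What the plan says.** **First administration.** Aim A2.2 (Protocol, Aims) has it done face to face for everyone: "Administer Life S-Can to all participants at the Clinical Trials Unit by a trained research dietitian".

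**Retest mode.** The Phase II methods give two accounts.
- The paragraph on the workflow of the validation study places the retest at the second visit, which "will also be at the Clinical Trials Unit and will take approximately 10-15 minutes". There, "Participants will be asked to return the accelerometer and complete the Life S-Can questionnaire again (reproducibility".
- The next numbered paragraph, on administering Life S-Can to the 100 survivors, says the retest may be done "either by phone or in person, to be convened with the patient".

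**Retest interval.** A2.2 says "Re-administer after 7-10 days for reproducibility analysis (test-retest method". The Phase II paragraph says "Participants will be offered to complete the Life S-Can questionnaire again after 10 days to test for reproducibility", with no upper limit. The accelerometer, whose return defines the second visit, follows the first of these: "it will have to be returned after 7-10 days" (Obtain objective measurements).

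**Analysis.** The Phase II statistics paragraph says "Pearson correlation and Intraclass correlation and Cohen’s Kappa will be used to test the relative validity, reliability and reproducibility of the screener". The protocol does not ask for the mode or the day of each retest to be recorded.

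**The concern.** A test-retest coefficient describes the error of the instrument only if the two occasions are otherwise alike. Here the first occasion is in person for all. If some second occasions are by phone, the difference between a person's two scores also contains any effect of changing mode. The pooled ICC and kappa cannot separate the two.

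The phone group would also not be a random subset, because the mode is arranged patient by patient. A later comparison of phone and in-person retests would be confounded with who ended up on the phone. If the mode is never recorded, even that comparison may be impossible.

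Reproducibility is an explicit part of the second specific aim, so what is at stake is one of the headline properties of the tool. The likely direction is a figure that is too low.

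**Working it through.** **1. The passages side by side**

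| Item | Aims, A2.2 | Phase II, workflow | Phase II, administration of Life S-Can |
|---|---|---|---|
| Retest mode | not stated separately | in person, visit 2 | phone or in person |
| Retest interval | 7-10 days | at accelerometer return (7-10 days) | after 10 days |

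The two Phase II paragraphs disagree on mode. On interval, a participant who returns the accelerometer and is retested on day 7 complies with A2.2 but not with the last column. All versions allow day 10.

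**2. What a mode change does to the ICC**

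The protocol states no target ICC, kappa or precision for the retest, so there is no figure to reproduce. Every input below is an assumption:
- ρ = 0.80, the ICC if everyone were retested in the same mode, with score variance 1 on each occasion;
- f, the share retested by phone;
- d, the mean shift caused by phone, in score SDs;
- s, the SD of person-to-person variation in that shift, in score SDs.

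The first occasion has variance v1 = 1. The second has v2 = 1 + f(1−f)d² + f·s². The mean difference between occasions is f·d. The absolute-agreement ICC is

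ICC = 2ρ / (v1 + v2 + (f·d)²).

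Because f(1−f)d² + f²d² = f·d², this reduces to

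ICC = 2ρ / (2 + f(d² + s²)).

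Two examples:
- f = 0.5, d = s = 0.5: 1.6 / (2 + 0.5 × 0.50) = 1.6 / 2.25 = 0.711.
- f = 0.1, d = s = 0.5: 1.6 / (2 + 0.1 × 0.50) = 1.6 / 2.05 = 0.780.

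| Phone share f | d = 0.3, s = 0 | d = 0.5, s = 0 | d = s = 0.3 | d = s = 0.5 |
|---|---|---|---|---|
| 10% | 0.796 | 0.790 | 0.793 | 0.780 |
| 30% | 0.789 | 0.771 | 0.779 | 0.744 |
| 50% | 0.782 | 0.753 | 0.766 | 0.711 |

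With a small shift (d = 0.2, s = 0) and half by phone, the result is 1.6 / 2.02 = 0.792.

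**3. Scale against sampling error**

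Using Fisher's transformation with standard error 1/√(n − 1.5), the approximate 95% interval for an ICC of 0.80 at n = 100 is 0.72 to 0.86. Only the most extreme cell (0.711) lies outside it. Sampling error is random, however, whereas the mode effect is systematic.

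**4. Interval**

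The documents give nothing from which to size an effect of retesting at day 7 rather than day 10 or somewhat later, so none is claimed. No kappa was computed, because the items and their categories are not yet fixed.

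**The case against.** The strongest reply is that phone retests will be few. Participants are expected at visit 2 anyway, and the phone option can be read as provision for those who cannot come. At 10% by phone the loss is 0.02 or less even with the large mode effect. This largely stands and sets the lower end of the range. It is not assured, though: the text does not call phone a fallback, and the accelerometer is itself only offered, so some participants may have less reason to return.

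A second reply is that the tool is meant to be flexible: self-administered or given by a professional, on phone, tablet or PC. Reproducibility across delivery conditions is then relevant. That is a fair question, but a separate one. A retest with unplanned mode changes in some participants neither tests equivalence between modes nor measures same-mode reliability cleanly.

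A third is that the analysis by mode can be left to the statistical analysis plan. The choice of coefficient and sensitivity analyses can. The mode, the timing and the recording of both are matters of conduct, and an analysis plan may not be able to recover what was never collected.

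Some stronger readings are not supported:
- A reader might infer that patients choose the mode freely. The text says only that it is arranged with them.
- A reader might infer that the differing intervals distort reliability. They meet at day 10, and accelerometer return points to 7-10 days.
- That sensitive items will be answered differently by phone is plausible, but the documents offer no evidence for it.
- That reproducibility could not be attributed to the tool at all goes too far. The probable error is a modest understatement, which would not falsely validate the screener.

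**Conclusion.** The contradiction on retest mode is real and lies in adjacent paragraphs of the same section. Because the first administration is in person for all, any phone retests mix mode differences into the ICC and kappa and would probably lower them.

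For an assumed same-mode ICC of 0.80, the loss is about 0.01-0.02 with few phone retests or a small shift. It rises to about 0.09 (0.80 to 0.711) if half are by phone with a 0.5 SD mean shift plus 0.5 SD person-level variation. That upper figure combines three unfavourable assumptions and is not a forecast; the protocol gives no basis for choosing within the range.

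The interval difference is a wording matter. Overall this is a cheap improvement and no threat to the validation study.

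**What to change.** 1. Make aim A2.2 and the two Phase II paragraphs agree: retest in person at visit 2, administered as on the first occasion, in one window of 7-10 days that matches accelerometer return. Say that this also applies to participants who decline the accelerometer.
2. Keep phone only as a fallback for those who cannot attend.
3. Record the mode and the day of every retest.
4. Base the main ICC and kappa on same-mode retests, with all retests as a sensitivity analysis. This step may sit in the statistical analysis plan.

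**Cost.** Protocol wording and two data fields; visit 2 is already planned. Phone retests leave the main estimate, so it describes attenders only and loses a little precision. With 90 instead of 100 same-mode pairs, the approximate 95% interval around an ICC of 0.80 goes from 0.72-0.86 to 0.71-0.86. With only 50 such pairs it would be 0.67-0.88, which is why phone should stay the exception.

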**3. Obtain objective measurements:**

- **Body weight and height** will be measured by a research dietitian at the Clinical Trials Unit.
- **Physical activity**: Physical activity, sedentary behaviour and sleep quality will be measured using an accelerometer. All participants will be offered to wear an accelerometer for 7 to 10 days. Accelerometry is one of the most reliable techniques for recording and storing the amount and level of physical activity performed by each person and in a given period of time. An accelerometer will be provided to the participant and it will be explained how to use it, and it will have to be returned after 7-10 days. These accelerometers are owned by the NUTRECOR research group and do not imply any added cost for the research group or for the participant. In addition, the use of an accelerometer constitutes a non-invasive technique.
- **Skeletal muscle mass and fat mass** Skeletal muscle mass and fat mass will be determined by a technician from the Nuclear Medicine Imaging Unit using DXA if possible, or using the bioimpedance measurement technique. DXA analysis is of interest to measure skeletal muscle accurately (in this case, for the interest of determining sarcopenia); however, it implicates a small exposure to radiation, similar to that of an X-ray. For this reason, participants will be given the option to either opt out of this procedure and/or analyze body composition via bioimpedance (which is less accurate for muscle mass).
- **Muscle function**: Muscle function will be determined using grip hand strength and the 30-s chair test.
- **Stress** will be measured by cortisol levels in the saliva samples brought in by the patient. Briefly, the salivary samples brought in by the participant will be stored at –80ºC and assayed for cortisol using an enzyme-linked immunosorbent assay kit following the protocol specified by Salimetrics. Samples will be assayed in duplicate.
- **(optional) Blood sample extraction:** All participants will be offered the option to provide a blood sample, which will be centrifuged to obtain blood specimens and will be stored at -80ºC for future studies in this cohort. This will be completely optional and will not determine participant inclusion in the study.

Staff from the Clinical Trials Unit will aid in sample obtention, processing and storing (research technicians) of all biological samples.

**Data integration and statistical analysis:** All data obtained using the questionnaires and the objective measurements will be integrated into a database. Any additional medical data needed will be obtained through medical records (prior consent by the participant). A data management plan following the FAIR principles will be established. Construct validity will be studied using the hypothetical latent structure, structural equation models and psychometric tests. Pearson correlation and Intraclass correlation and Cohen’s Kappa will be used to test the relative validity, reliability and reproducibility of the screener. Internal consistency of the screener will be analysed using Cronbach Alpha.

**PHASE III. PILOT INTERVENTION STUDY**

Phase III is divided into three stages: intervention design, patient recruitment (in combination with Phase II) and group allocation and intervention. Participation in this study will entail visits to the Clinical Trials Unit at IdISBa, located within the Hospital Universitari Son Espases. When possible, visits will be coordinated with other routine appointments at the hospital in order to reduce as much as possible the burden on the participant.

1. **DESIGN OF INTERVENTION**

The intervention will be designed using multidisciplinary approach, whereby knowledge and expertise in oncology, nutrition, epidemiology, psychology and psychometry, validation and implementation will be called upon. In addition, the views and experiences of cancer patients and patient organizations are essential in designing an effective intervention; hence non-scientific authors will be contacted and included in this phase. Close collaboration between patients, organizations, researchers, clinical fellows and institutions is crucial for this project.

The design of the intervention will be developed as follows:

**Recruit an expert panel:** Together with the Principal Investigator, five key personnel have been listed in this project, all of whom carry out research at the Health Research Institute of the Balearic Islands (IdISBa, Spain) together with other duties (university professor, medical doctor). Key personnel not contemplated as researchers in this project include international experts in nutrition and cancer with whom the PI and [name] have previously collaborated with (*detailed below in “Collaborations involved in the project”*), and will be consulted throughout the project. Cancer survivors will also be contacted at this stage (either through patient-orientated organizations or the hospital) to involve them in the design stage.

**Elements of the intervention at discussion:** A series of meetings, semi-structured interviews and panel groups will be planned with expert panel members and non-scientific actors to define the best intervention. Elements to be defined during this stage are: scoring of the individual domains of Life S-Can herein studied and traffic-light system (good, intermediate and non-adherence, which will direct the intervention and health professionals to be visited), monitoring of patients, pipeline, feedback, appointment system, Clinical Trials Unit and data collection.

**Groups of intervention:** A random allocation system will be applied to participants. Participants allocated to the Control Group will receive the first, baseline visit offered to all participants (described in Phase II, validation study) with a trained dietitian, who will administer the Life S-Can questionnaire and a series of validated questionnaires, and then will be given the results of the screener, but no specific feedback will be given other than the standard care and recommendations already provided by the Oncology Department.

The intervention still needs to be defined; however participants allocated to the Intervention Group will receive a baseline visit with a trained dietitian, who will administer the Life S-Can and depending on the score obtained in the domains of diet, physical activity and psychosocial concerns, the participant will likely be offered to see an oncological dietitian (diet domain), a physiotherapist (physical activity) and/or a psychologist (psychosocial distress) for up to three visits (one individual, two group sessions).

All participants will attend a final visit after 3 months to collect data on feasibility, acceptability and efficacy of the intervention.

1. **RECRUITMENT OF PARTICIPANTS**

Cancer survivors (n=100) will be recruited by the Oncology Department at the HUSE as explained in Phase II.

1. **INTERVENTION STUDY**

The intervention study herein proposed will be defined by an expert panel and non-scientific actors as abovementioned; however, we can envision how it may look like. It may consist of 5 visits maximum over 3 months: one baseline visit for all participants, up to three visits for participants from the intervention group (depending on the care plan designed) and one final visit for all participants from both groups. All visits will be carried out at the Clinical Trials Unit at IdISBa (located in HUSE) and will be monthly (one visit per month) (Figure 2). Visits will be coordinated by the PI of the project, together with other team members ([name], [name]). Dietary, physical activity and psychologic interventions will be carried out by in-house researchers (trained oncological dietitian – [name], and others as part of [name]’s NUTRECOR team) and external health professionals (accounted for in the budget of the obtained funding: INSPIRE (World Cancer Research Fund) and IMPETUS (IdISba, #IMP23/01).

[figure not shown]

